## Abstract

**Background:** Crohn’s disease (CD) is an inflammatory bowel disease in which there is an alteration in the homeostasis and functionality of the intestinal mucosa accompanied by a dysbiosis of the commensal microbiota. The analysis of different dietary strategies to achieve CD remission and reduce gastrointestinal symptoms concludes that it is necessary to restrict the intake of ultra-processed products and to promote the consumption of those with anti-inflammatory effects that improve intestinal permeability and dysbiosis. **Methods:** Based on previous studies conducted in other cohorts, mainly pediatric, we propose an experimental, prospective, randomized study in patients with active CD who do not show improvement with conventional pharmacological treatment. The control group will receive standard nutritional recommendations while the intervention group will be prescribed an exclusion diet supplemented with enteral nutrition. **Results:** Patients in the intervention group are expected to exhibit increased lean body mass and reduced visceral fat, as measured by bioelectrical impedance analysis (BIA), alongside higher rates of clinical remission (CDAI), decreased inflammatory markers, and improved gut microbiota composition. Additionally, improvements in health-related quality of life are anticipated, as assessed by validated questionnaires. **Conclusions:** In the present project, we plan to conduct a detailed study to determine the potential of the exclusion diet for the treatment and remission of CD in adult patients, with the hypothesis that this nutritional intervention will be able to modify and improve intestinal dysbiosis, inflammatory status, and clinical and body composition markers in these patients.

## 1. Introduction

Crohn’s disease (CD) is a chronic, relapsing-remitting inflammatory disorder characterized by intestinal lesions that may appear discontinuously anywhere along the gastrointestinal tract, potentially causing chronic abdominal pain, diarrhea, intestinal obstruction, and/or perianal lesions [1].

Its multifactorial etiology results from the interaction of genetic factors, the immune system, and the individual’s commensal microbiome [2]. In turn, these are influenced by environmental factors (diet, pollution, lifestyle habits), which give rise to an aberrant response and the consequent intestinal inflammation characteristic of the disease [2].

Therefore, the development of diets aimed at modifying the gut microbiome has emerged as a promising strategy to improve the management and evolution of CD, as most drug therapies are associated with significant health costs and side effects due to their immunosuppressive role that may affect the overall health of the patient [3]. These factors, coupled with the fact that there is a considerable rate of CD patients who do not show an adequate therapeutic response to monoclonal antibodies, make absolutely necessary the development of new, less aggressive but more effective strategies to improve the quality of life of CD patients [3].

The analysis of various dietary strategies addressed to achieve remission of CD and reduce gastrointestinal symptoms concludes that it is necessary to restrict the intake of ultra-processed products while promoting foods with anti-inflammatory effects that improve intestinal permeability and dysbiosis [4,5]. The European Society for Clinical Nutrition and Metabolism (ESPEN) acknowledges that there is insufficient evidence to recommend a specific diet and emphasizes the importance of individualization. The current scientific literature supports the use of the exclusion diet (ED) in CD, which is characterized by the exclusion of frozen or packaged foods due to their additive content and the inclusion of fresh, fiber-rich foods, owing to the benefits observed in symptom remission in the pediatric population [6].

However, evidence in adults, although encouraging, remains limited [5]. The ED is supplemented with a specific enteral nutrition formula that should not exceed 1250 Kcal/day and is administered at a proportion of 25–50%, depending on the phase of the diet. The first two phases last 6 weeks each (12 weeks in total) and include foods that must be consumed daily. In the final maintenance phase, starting from week 13, there are no mandatory foods, and a Mediterranean diet is promoted [7]. The literature also advocates for modifying the dietary pattern by reducing ultra-processed foods and adhering to the Mediterranean diet after one year of initiating the ED [7,8].

On the other hand, evidence regarding the impact on body composition in patients with CD is scarce and heterogeneous, which justifies further research and the publication of higher-quality data [9,10]. These findings could present an opportunity to improve the treatment of patients with CD and to incorporate body composition assessment into routine clinical practice.

In the present clinical trial, we propose to conduct a detailed study to determine the potential of the exclusion diet for the treatment and remission of CD in adult patients, with the hypothesis that this nutritional intervention will be capable of modifying and improving intestinal dysbiosis, the inflammatory state, and both clinical and body composition markers in these patients. By assessing the impact of the exclusion diet not only on clinical remission and inflammation, but also on body composition, this study addresses multiple unmet clinical needs: it tests a low-risk, non-invasive therapeutic strategy; explores its relationship with the microbiota; and introduces a precision nutrition approach to the treatment of CD. Together, these aspects position this study as a significant contribution to the advancement of personalized medicine in CD.

## 2. Materials and Methods

### 2.1. Study Objectives

The primary objective of this clinical study is to determine the effectiveness and impact on body composition of implementing an ED for symptomatic remission in adult patients with active CD.

To achieve this objective, five specific aims are defined:To assess the improvement of clinical and inflammatory parameters related to the progression of the disease.To evaluate the incidence of sarcopenia through the assessment of muscle strength, function, and composition using functional tests, dynamometry, bioelectrical impedance analysis (BIA), and nutritional ultrasound.To determine the rate of improvement in the quality of life of patients and the disease remission by evaluating the Crohn’s Disease Activity Index (using the CVEII9 quality of life questionnaire and the Harvey–Bradshaw Index).To analyze the modifications in the intestinal microbiota resulting from the implementation of the ED.To examine the progression of clinical, anthropometric, analytical, and body composition parameters.

### 2.2. Design

This is an experimental, prospective, randomized study with matched data, including patients with CD who are either about to begin pharmacological treatment or are scheduled to have their medication changed due to an insufficient response and lack of positive disease progression. The pharmacological treatment will be prescribed based on clinical indications by the medical team at baseline and will not be influenced by whether the exclusion diet is implemented.

### 2.3. Study Setting

Study participants will comprise adult patients of both sexes recruited by the Endocrinology and Nutrition Service at the Virgen de la Arrixaca University Clinical Hospital (HCUVA). These participants will be selected from individuals previously diagnosed with CD by the hospital Digestive System Service who satisfy the eligibility criteria of the study. Upon signing the informed consent document and after confirming that all inclusion criteria are met—with no exclusion criteria present—the patient will be deemed eligible for enrollment in the study. Subsequently, each enrolled patient will be assigned a unique, consecutively numbered identifier.

### 2.4. Eligibility Criteria

#### 2.4.1. Inclusion Criteria

The following criteria must be met for inclusion in this study:Subjects of both sexes over 18 years of age.A diagnosis of active luminal CD with small bowel involvement, with or without colonic involvement, prior to study inclusion.Active symptoms of CD at the time of initiation of the nutritional intervention.Active disease, defined as a Harvey–Bradshaw Index (HBI) > 4 and an objective measure of disease activity, such as an elevated inflammatory marker (CRP > 5 mg/L or 0.5 mg/dL, or calprotectin ≥ 250 µg/g) and/or a radiological imaging test (MR enterography or intestinal ultrasound) or an endoscopic test (ileocolonoscopy or capsule endoscopy).Ability and willingness to adhere to one of the nutritional interventions.Capacity to complete and sign the informed consent form.

#### 2.4.2. Exclusion Criteria

Patients who fulfill any of the following criteria will be excluded from this study:Patients experiencing a severe flare associated with fistulizing tracts or strictures during the study period.Hospitalized patients.Patients with known intolerance or hypersensitivity to the components of the nutritional supplement Modulen IBD.Patients following another diet or who are participating in other nutritional trials.Patients scheduled for surgical intervention during the study period.Patients with active malignancy.Patients under treatment with antibiotics or probiotics.Patients with other clinical conditions that may interfere with the implementation of the planned nutritional interventions (such as heart disease, celiac disease, uncontrolled diabetes, active infections, tuberculosis, or a positive stool test for Clostridium difficile toxin).

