### 2.12. Randomization and Blinding

Patients will be randomized in a 1:1 ratio after meeting the study inclusion and exclusion criteria. In the control group, patients will receive standard nutritional recommendations, whereas in the intervention group, they will follow a dietary strategy based on partial enteral nutrition combined with an exclusion diet, which has been shown to be effective in inducing remission, promoting mucosal healing, and serving as a rescue therapy for patients with inadequate response to biologic treatments.

Patients in the intervention group will be required to maintain this dietary strategy for 12 weeks, with structured follow-up visits at 6, 12, 24, and 48 weeks. Subsequently, patients should continue with the maintenance phase starting from week 13 onwards. Nutritional intake will be adjusted to ensure a balanced provision of macronutrients and essential micronutrients, prioritizing the inclusion of key substrates for short-chain fatty acid production while avoiding foods and additives with potential pro-inflammatory effects.

Simple randomization will be computer-generated and conducted by a member of the research team at the study site. Due to the nature of the intervention, neither patients nor research or medical staff will be blinded. Group assignment will be disclosed to patients at the moment of their participation acceptance.

Furthermore, to minimize the risk of bias, the clinicians from the Gastroenterology Department responsible for performing imaging assessments, as well as the translational researchers from the Biomedical Research Institute of Murcia (IMIB) in charge of analyzing blood, urine, and stool samples, will remain blinded to the dietary allocation of the study participants.

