### 2.13. Data and Sample Collection and Analysis of Variables

#### 2.13.1. Data Collection

Data and biological sample collection will be conducted prior to the initiation of the nutritional intervention (baseline) and throughout the intervention during scheduled follow-up visits at 6, 12, 24, and 48 weeks. A comprehensive clinical assessment will be performed, encompassing the collection of anthropometric data (height, weight, body mass index), detailed records of patient medication, and evaluation of dietary intake using a 24 h dietary recall and Food Frequency Questionnaires (FFQs). Additionally, validated instruments will be employed to assess quality of life (CVEII-9) [Figure 2] and physical activity levels (IPAQ) [Figure 3].

The use of Mediterranean diet adherence questionnaires (PREDIMED) [Figure 4], the 24 h dietary record, and Food Frequency Questionnaires (FFQs) are useful tools for assessing adherence to the Mediterranean diet. However, they are not without limitations, as they may not capture inter-individual variability in diet or may be misinterpreted by subjects. Measurement of certain biomarkers that increase during a Mediterranean diet (such as carotenoids, n-3 fatty acids, and/or monounsaturated fatty acids) may be a more objective alternative to assess dietary adherence [13].

Body composition and functional changes will be analyzed using biochemical parameters associated with the underlying pathology and the patient’s general health status. Functional performance tests, including dynamometry, BIA, and nutritional ultrasonography, will be conducted to evaluate morphofunctional alterations. A comprehensive nutritional and morphofunctional assessment will be repeated three months following the conclusion of the dietary intervention.

Clinical remission will be evaluated using the Harvey–Bradshaw Activity Index (score < 5) and fecal calprotectin levels (<250 µg/g). At weeks 24 and 48, the radiological imaging study performed at baseline (e.g., MRI enterography or intestinal ultrasonography) will be repeated and/or an intestinal biopsy may be performed to objectively confirm remission of CD.

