## 3. Discussion

The findings of this study could contribute to the implementation of nutritional therapy in adult patients with active luminal CD (non-stricturing, non-penetrating) of the small intestine, with or without colonic involvement, who are initiating treatment with biologic agents or JAK inhibitors. Partial enteral nutrition (PEN) combined with the exclusion diet (ED) has demonstrated efficacy in inducing remission in both pediatric and adult patients, promoting mucosal healing and serving as a rescue therapy for patients who fail biologic therapy [11,12].

In this context, the Crohn’s Disease Exclusion Diet (CDED) has emerged as a promising whole-food-based dietary intervention, specifically designed to reduce exposure to dietary components that impair the intestinal barrier and alter the gut microbiome. In a pivotal 12-week prospective randomized trial, Levine et al. compared CDED combined with partial enteral nutrition (PEN) to exclusive enteral nutrition (EEN) in children with mild to moderate CD [12]. The study showed that CDED + PEN was significantly better tolerated than EEN (97.5% vs. 73.6%, *p* = 0.002), and while both approaches achieved comparable remission rates at week 6, sustained corticosteroid-free remission at week 12 was notably higher in the CDED + PEN group (75.6% vs. 45.1%, *p* = 0.01) [14]. Additionally, the CDED + PEN group exhibited sustained reductions in inflammatory biomarkers and favorable modulation of the fecal microbiota [12]. These findings support the clinical utility of CDED + PEN as a more tolerable and effective strategy for inducing and maintaining remission in pediatric CD. Recent clinical data on adult patients reinforce the efficacy of CDED beyond pediatric populations. In a study involving 32 participants (18 women and 14 men), clinical remission was achieved in 76.7% of patients at 6 weeks and in 82.1% at 12 weeks of therapy [11]. Furthermore, fecal calprotectin levels showed a significant reduction by the second follow-up time point compared with baseline (*p* = 0.021) [11]. These findings suggest that CDED is also an effective therapeutic option for inducing remission in adult patients with CD.

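### The severe-flare exclusion criterion is timed to the study period rather than to screening, so read literally it allows removal after randomisation and loss of the outcomes that would record the failure

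*Protocol article*

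**What the plan says.** The list in section 2.4.2 opens with "Patients who fulfill any of the following criteria will be excluded from this study". Its first item is "Patients experiencing a severe flare associated with fistulizing tracts or strictures during the study period".

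Two other sections say when the criteria apply. Section 2.3 has a patient deemed eligible for enrolment after consent and confirmation of the inclusion criteria, "with no exclusion criteria present". Section 2.12 says "Patients will be randomized in a 1:1 ratio after meeting the study inclusion and exclusion criteria". Table 1 ticks the eligibility check only in the pre-diet column. The same table is headed with the term study period, and its columns run from that pre-diet visit to week 48. Section 2.12 sets "structured follow-up visits at 6, 12, 24, and 48 weeks" and states that "neither patients nor research or medical staff will be blinded". Imaging and laboratory assessors are blinded.

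Section 2.5 says that participants who withdraw are not followed further and not replaced. Data gathered before withdrawal stay in the analysis and none are gathered afterwards. Section 2.6 lists the grounds for withdrawal. A severe flare is not among them, but an adverse event that the investigator judges to require withdrawal is.

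On phenotype, section 2.4.1 asks for active luminal disease with small bowel involvement. The Discussion describes the target population as "adult patients with active luminal CD (non-stricturing, non-penetrating) of the small intestine".

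**The concern.** An eligibility criterion has to be decidable before allocation. A severe flare over the following 48 weeks is not: it is a form of treatment failure and could be affected by the diet under test. If the criterion is applied as worded, a participant whose disease worsens in this way at, say, week 20 meets a ground for exclusion. The week 24 and 48 assessments would then be missing for exactly those patients most likely to fail them. Remission is defined by a Harvey–Bradshaw score below 5 with calprotectin below 250 µg/g, and imaging is repeated at those two visits.

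The treating and research staff know the allocation, and section 2.4.2 does not define a severe flare, so the decision to apply the criterion could also vary with the arm. The comparison at stake is the remission comparison in the primary objective. There is a second, smaller issue: the criteria do not spell out the phenotype that the Discussion names.

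**Working it through.** **1. Can the criterion be applied in the protocol's own sequence?**

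| Place | What it fixes |
|---|---|
| 2.3 | No exclusion criterion present at enrolment |
| 2.12 | Randomisation follows the eligibility check |
| Table 1 | Eligibility ticked at the pre-diet visit only; study period runs to week 48 |
| 2.4.2, first item | Flare at any time in the study period |

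The last row cannot be satisfied at the time set by the first three. The surgery item in 2.4.2 uses the same time phrase, but it concerns operations already scheduled, which can be known at screening. The inclusion criteria in 2.4.1 anchor timing explicitly, to before inclusion or to the start of the diet. The flare item lacks such an anchor.

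**2. What is lost if the criterion is used after randomisation?** The article does not describe post-randomisation exclusion separately, so section 2.5 is the nearest rule. Under it, a participant removed at week 20 keeps the week 6 and week 12 data and loses weeks 24 and 48. The end of the 12-week diet is unaffected for that participant.

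**3. How large could the effect be?** The document gives no flare rate, so everything here is illustration. Let p be true remission among all randomised at a visit after the flare, and f the share removed by then, all non-remitters. If the removed patients are left out at that visit, observed remission is p/(1 − f).

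With p = 0.50 in both arms:
- f = 0.05: 0.50/0.95 = 52.6%
- f = 0.10: 0.50/0.90 = 55.6%
- f = 0.15: 0.50/0.85 = 58.8%
- 15% v 5%: 58.8 − 52.6 = 6.2 points, in favour of the arm with more removals
- 5% v 5%: no difference; both arms read 2.6 points too high

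In whole patients, with the 48 per group of section 2.11 and 22 remitters in each arm (45.8%), removing 7 v 2 gives 22/41 = 53.7% v 22/46 = 47.8%, a difference of 5.8 points.

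False-positive rate at such a visit, from a pooled two-sided 5% test with 48 per arm before removal and equal true remission:

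| True remission | Removed | Observed | Difference (points) | Type I error |
|---|---|---|---|---|
| 45% | 5% v 5% | 47.4% v 47.4% | 0 | 5.0% |
| 45% | 10% v 5% | 50.0% v 47.4% | 2.6 | 5.7% |
| 45% | 15% v 5% | 52.9% v 47.4% | 5.6 | 8.1% |
| 60% | 10% v 5% | 66.7% v 63.2% | 3.5 | 6.4% |
| 60% | 15% v 5% | 70.6% v 63.2% | 7.4 | 11.2% |

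Swapping the arms reverses the sign.

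**4. Sample size.** The point does not depend on it. The dropout step reproduces: 48/0.95 = 50.5, so 51, inside the planned 50–55. The 48 itself cannot be reproduced because section 2.11 states no effect size.

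**The case against.** The strongest reply is that this is a baseline criterion, loosely worded. It sits under eligibility, sections 2.3 and 2.12 place the check before allocation, and no section says that exclusion criteria are applied again later. Removal after randomisation has its own list in section 2.6, which names neither a flare nor later failure of an exclusion criterion. The pre-diet visit is itself part of the study period in Table 1, so a patient flaring at that visit fits the words. This reading is plausible. It does not make the text correct, because the phrase still covers the visits up to week 48 and nothing limits it to screening.

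A reader might infer three stronger things that the documents do not support:

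- **That the plan deletes failures from the analysis.** It does not say so. Section 2.5 retains data up to withdrawal, so at most the later visits are lost. How missing visits are handled may be settled in an analysis plan that is not shown.
- **That the remission comparison is biased by 6 points.** That figure needs a three-fold imbalance in removals, no remitters among those removed, and their omission at visits after the flare. None of these is in the document.
- **That stable stricturing or fistulising disease is freely eligible.** Section 2.4.1 requires luminal disease, and the Discussion glosses that word as non-stricturing and non-penetrating. The phenotype is implied, though not stated as a criterion.

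It is also true that the adverse-event and investigator-discretion routes in sections 2.5 and 2.6 would remain if only the criterion were reworded. That is why the fix needs a sentence on follow-up as well.

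**Conclusion.** The point holds as a contradiction in timing with a possible consequence for the data. The criterion as worded cannot be applied when the protocol says it must be. Followed literally, it opens a route to outcome-dependent loss of follow-up in a trial where patients and treating staff know the allocation.

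Neither the size nor the direction of any bias can be fixed from the document. It is zero from this source if removal and remission are equal across arms. It is about 6 points at visits after the flare under 15% v 5% removal, no remitters among those removed and 50% true remission. The results vary with the assumed rates as tabulated. Data from visits before the flare are not affected.

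Because a baseline intention is plausible and earlier data are kept, this ranks as a correction worth making rather than one on which the trial's validity turns.

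**What to change.** 1. State in section 2.4.2 that all exclusion criteria, including this one, are assessed at screening, before randomisation, and are not applied again afterwards. For this item, replace the time phrase with presence at screening.
2. Reconcile sections 2.4.1, 2.4.2 and the Discussion on whether stricturing or penetrating disease is eligible, so that the enrolled population is the one the conclusions will describe.
3. Add to section 2.5 or 2.15 that a participant who has such a flare after randomisation stays in follow-up where consent allows, is analysed in the assigned arm, and counts as not in remission from that visit. This concerns follow-up and analysis only. It leaves clinical management of the flare untouched.

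The cost is a few sentences, any approval that section 2.9 requires, and continued visits for the patients concerned. The sample size does not change. The downside is a slightly lower reported remission rate. With equal true remission and this rule in force, this source adds no difference between arms and the type I error stays at 5%. The change is best made before follow-up is under way, because visits that were never held cannot be recovered.
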